# Anal fistulotomy with one-stage shaped skin grafting for intersphincter anal fistulas: study protocol on a multicentre randomised controlled trial

**DOI:** 10.1186/s13063-023-07495-7

**Published:** 2023-07-22

**Keywords:** Anal fistula, Anal fistulotomy, Randomised controlled trial, Skin graft

## Abstract

**Background:**

Anal fistulas are mainly treated via surgery. They can be difficult to treat without surgical intervention. Numerous procedures, such as fistulectomy and fistulotomy, are performed to treat anal fistulas and achieve good effects. However, the wounds created through fistulectomy and fistulotomy take a long time to heal. Therefore, a multicentre randomised controlled trial (RCT) is proposed to study the efficacy of one-stage shaped skin grafting at the surgical wound to heal low simple intersphincter anal fistulas.

**Methods:**

This study is a multicentre, hospital-based RCT. It will be performed at three hospitals. A total of 104 patients with low simple intersphincter anal fistulas who meet the inclusion criteria will be included in this trial and will be allocated randomly to two groups (test and control groups). The patients in the test group will receive one-stage anal fistulotomy surgery combined with shaped skin grafting, and those in the control group will undergo anal fistulotomy only. All the operations will be performed by attending colorectal surgeons or surgeons of a higher level. Effectiveness and safety indicators will be observed, recorded and analysed.

**Discussion:**

Anal fistulotomy can heal low simple intersphincter anal fistulas effectively and safely with a low recurrence rate. Skin grafts promote wound epithelisation significantly. We believe that skin grafting can treat low simple intersphincter fistulas with a short healing time.

**Trial registration:**

Chinese Clinical Trial Register, ChiCTR2000039174. Registered on 28 October 2020.

## Introduction

### Background and rationale

Anal fistulas, which are common in colorectal diseases, affect approximately 1/10,000 of the normal population every year, according to Corson’s report [1]. A fistula is a pathological connection between two epithelialised openings. An anal fistula is a granulation tract between the anal canal or rectum and the skin around the anal verge. Approximately 80% of anal fistulas develop secondary to cryptogenic abscesses arising from infected anal glands, which can spread to other parts in many directions and represent chronic perianal sepsis conditions [1].

A series of surgical or nonsurgical therapeutic options for anal fistulas have been developed. Nonsurgical methods include antibiotics, anal fistula plugs and fibrin glue. Numerous surgical procedures are available and include two types: impairing or reserving the anal sphincter, such as laying the anal sphincter open, fistulotomy, fistulectomy, loosening or cutting the seton, ligating the intersphincteric fistula-tract, video-assisted anal fistula treatment and fistula-tract laser closure. However, the ideal surgical technique for anal fistula treatment should aim to deracinate the internal opening, which often leads to sepsis, and the granulation tract then promote postoperative wound healing while preserving sphincter function and anal continence because maintaining normal continence relies on the complex interaction of the anal sphincter and pelvic floor innervations [2]. Procedures for impairing and preserving anal sphincters in anal fistulas have postoperative recurrence rates of 0–65% and incontinence rates of 0–63%. In radical techniques that involve cutting additional anal sphincter muscles, the recurrence rate decreases, and the incontinence rate increases accordingly [3]. Laying simple and low anal fistulas open directly is relatively effective and safe and is widely accepted by surgeons [4]. Anal fistulotomy, which involves the division of pathogenic tracts, has been applied to treat subcutaneous and intersphincteric anal fistulas and has an excellent healing rate of over 90% [3, 5]. However, the risk of faecal incontinence increases with the extent of the division of the external anal sphincter [6–8].

In addition to concerns about anal sphincter damage and even faecal incontinence, long postoperative wound healing times are another major challenge posed by anal fistula surgeries. Most techniques have wound healing times of approximately 4 weeks, and some even have wound healing times of 8 weeks. In Ahmed’s study, the patients who received one-stage fistulectomy had average wound healing times of approximately 3–4 weeks [9]. The continuous purulent discharge of the wound and other complications during wound healing may make the patient uncomfortable, affect their quality of life considerably and even delay their return to work.

Anal fistulotomy is an effective and safe technique for the treatment of simple and low anal fistulas. It has a healing rate of over 90%. However, its postoperative recovery time, especially its wound healing time, is very long. We have made some attempts to shorten the wound healing time of this technique. Our early observations showed that skin grafting at the wound area after fistulotomy promotes wound healing significantly. We grafted full-thickness skin from the area of the anal fistula and then performed a fistulotomy in one stage. We anticipate that this technique will shorten wound healing time because numerous studies have demonstrated that skin grafting is an effective treatment for the rapid coverage of ulcers [10]. A multicentre randomised controlled trial (RCT) is proposed to study the efficacy of the method of one-stage anal fistulotomy with shaped skin graft (SSG) at the surgical wound to heal low simple intersphincter anal fistulas and confirm our supposition about this method.

### Objectives

This trial aims to confirm the efficacy of one-stage SSG at the surgical wound after anal fistulotomy for low simple intersphincter anal fistulas.

### Trial design

This randomised, double-blinded, parallel, superiority trial will be completed at three research centres, including the First Affiliated Hospital of Guangzhou University of Chinese Medicine (GZUCM), Wuyi Hospital of Traditional Chinese Medicine and Dongguan People’s Hospital, over 2 years. A total of 104 patients with low simple intersphincter anal fistulas who meet the study criteria will be randomised (1:1) to the test and control groups. The intervention will last for the whole duration of the hospital stay with a follow-up of 6 months. Informed written consent will be obtained prior to the commencement of this study. All enrolled subjects will be fully informed about the purpose, process and possible risks of the study.

## Methods: participants, interventions, and outcomes

### Study setting

The study will be completed at three research centres.

### Eligibility criteria

Patients with low simple intersphincter anal fistula (Fig. 1) will be enrolled from the First Affiliated Hospital of GZUCM, Wuyi Hospital of Traditional Chinese Medicine and Dongguan People’s Hospital.

**Fig. 1 Fig1:**
[figure not shown]
Low simple intersphincter anal fistula

#### Inclusion criteria

Patients who received rectal–anal magnetic resonance imaging (MRI) examination and were diagnosed with low simple intersphincter anal fistula in accordance with ‘Chinese Colorectal and Anal Surgery’ compiled by Wang Jianping and published by People’s Medical Publishing House in 2014.Patients aged between 18 and 60 years.Patients with normal anal morphology and function and without anal abnormality and incontinence.Patients with internal and external openings and tract distribution between 5 and 7 o’clock around the anal verge in the lithotomy position.Patient with body mass index (BMI) < 30.Patients who agreed to participate voluntarily in this study, signed an informed consent form, and had good compliance. For example, patients who can understand the study, agreed to accept and complete all the interventions of the study, and can be followed up in the stipulated timeframe.

#### Exclusion criteria

Patients with anal trauma, inflammatory bowel disease, malignant tumours, HIV, tuberculosis, actinomycotic infection and other perineal complications.Special patients who are pregnant and lactating or patients with respiratory, digestive, circulation, blood system disorders, liver and kidney dysfunction or other disorders.Patients with diabetes and/or other special factors (radiation damage and burns) that affect wound healing.Patients who are under acute perianal sepsis conditions.Patients with abnormal anal morphology and function.Patients whose internal opening and tract are above the dental line by over 1 cm.Patients with more than one internal or external opening and tract.Patients with contraindications to MRI.Patients who cannot understand and disagree to join the study and cannot be followed up.

#### Withdrawal criteria

Patients who do not meet the inclusion criteria after inclusion in the study.Patients who are not given the established treatment of the study.Patients without personal information or with untruthful personal information.Patients with serious adverse reactions during treatment, who voluntarily quit or who are found to be ineligible for the study by the investigators.Patients without any treatment after inclusion.

### Who will collect informed consent?

Written informed consent from potential trial participants or authorised surrogates will be obtained by a colorectal surgeon at three research centres.

### Additional consent provisions for the collection and use of participant data and biological specimens

Not applicable.

## Interventions

### Explanation for the choice of comparators

Although anal fistulotomy is effective and safe, its postoperative recovery time, especially wound healing time, is very long. Our early observations showed that grafting at the wound shortened the wound healing time significantly compared with the technique without grafting. We proposed this study, which aims to compare anal fistulotomy with grafting with anal fistulotomy without grafting, to confirm our findings on grafting. A total of 104 patients with low simple intersphincter anal fistulas who meet the study criteria will be randomised (1:1) to the test and control groups.

### Intervention description

The patients in the test group will receive one-stage anal fistulotomy surgery combined with SSG, and those in the control group will undergo anal fistulotomy only. All the operations will be performed by attending colorectal surgeons or surgeons at a higher level. During this trial, all subjects will receive general treatment.

The patients in the test group will be on a semiliquid diet and take oral polyethylene glycol electrolyte powder for bowel preparation one night before operation. The patients will be placed in the lateral position after spinal anaesthesia, and their perianal skin will be sterilised. Their tract and internal opening will be probed by using a probe. Then, a strip of skin with a size of 1. 0 cm × 3.0 cm will be incised and freed below the dental line along the fistula and distal to the outer side of the anus without cutting its end (Figs. 2 and 3). The probed tract will be opened and scraped (Figs. 4 and 5), and the inflamed tissue will be removed. Some tissue will be retained for biopsy. Wound bleeding will be stopped by electrocoagulation if necessary, making the harvested skin from the surgical region into full-thickness skin (Fig. 6) and grafting it at the wound closely without tension by stitching with 4–0 Coated Vicryl (Figs. 7 and 8). The wound will be covered with petrolatum gauze and sterilised dressing. All the patients will be given celecoxib one piece at a time twice a day to relieve pain for 7 days. Patients will be advised to go on semiliquid diets and control bowel movements for 3 days. The wound will be cleaned gently with warm water after every bowel movement. Patients will be followed-up on the 3rd day, 7th day, 14th day, 21–22nd day, 27–29th day, 2nd month, 3rd month and 6th month postoperation in clinic visits.

**Fig. 2 Fig2:**
[figure not shown]
Incision and freeing of the skin

**Fig. 3 Fig3:**
[figure not shown]
Incision and freeing of the skin

**Fig. 4 Fig4:**
[figure not shown]
Opening of the tract

**Fig. 5 Fig5:**
[figure not shown]
Scraping of the wound

**Fig. 6 Fig6:**
[figure not shown]
Obtaining full-thickness skin

**Fig. 7 Fig7:**
[figure not shown]
Grafting of the skin

**Fig. 8 Fig8:**
[figure not shown]
Completing the procedure

The control group will be placed on the same diet and undergo the same preoperation bowel preparation as the test group. The patients in this group will receive a fistulotomy from eligible colorectal surgeons. Other postoperative treatments, such as changing wound dressing and follow-ups, are also the same.

### Criteria for discontinuing or modifying the allocated interventions

Rejection criteria: (1) Patients who do not meet the inclusion criteria after inclusion in the study. (2) Patients who are not given the established treatment of the study.

Shedding criteria: (1) Serious adverse reactions related to the study procedure. (2) Major mistakes in the clinical research protocol that make evaluating the efficacy of the technique difficult. Observation of a significant deviation in the implementation of a well-designed protocol.

Subject termination criteria: (1) Subject terminates spontaneously (e.g. withdrawal of informed consent). (2) Subject uses a combination of drugs or undergoes other operations within a nonprescribed range that may affect the judgement of efficacy and safety. (3) Indices of liver function: transaminase ≥ 3 times the upper limit of normality for > 1 week. Indices of renal function: Cr ≥ 1.2 times the upper limit of normality for > 1 week. (4) Subject develops adverse events or their condition worsens, leading the investigator to decide that the subject has to quit early. (5) Other investigators consider that the subject is unsuitable to continue and needs to quit. (6) Subjects who voluntarily quit or are found to be ineligible for the study by the investigators.

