### Analysis methods for handling protocol nonadherence and any statistical methods for handling missing data

Study populations include the intent-to-treat analysis set defined as all randomised patients and the per-protocol analysis set defined as all patients in the intent-to-treat population without any major protocol deviations. Multiple imputations will be used to manage missing values.

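### Outcome-related withdrawal and termination rules are not reconciled with the all-randomised ITT set, so likely failures can go unobserved and then be imputed

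*Protocol article*

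**What the plan says.** Two sections of the protocol article list grounds for taking a patient out after inclusion.

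- **Withdrawal criteria.** The list includes "Patients who are not given the established treatment of the study" and "Patients with serious adverse reactions during treatment, who voluntarily quit or who are found to be ineligible for the study by the investigators". It also names patients who receive no treatment at all.
- **Criteria for discontinuing or modifying the allocated interventions.** The rejection criteria repeat ineligibility and non-receipt of treatment. The shedding criteria include serious adverse reactions tied to the procedure. The termination criteria include a patient who "undergoes other operations within a nonprescribed range that may affect the judgement of efficacy and safety" and the ground "Subject develops adverse events or their condition worsens, leading the investigator to decide that the subject has to quit early".

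Under Adverse event reporting and harm (Medical treatment), the investigator who finds an adverse reaction also decides whether observation ends.

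The section on nonadherence and missing data says: "Study populations include the intent-to-treat analysis set defined as all randomised patients". The per-protocol set is "all patients in the intent-to-treat population without any major protocol deviations". On gaps it says: "Multiple imputations will be used to manage missing values".

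The article does not say whether a withdrawn, rejected, shed or terminated patient goes on giving outcome data. It does not say how worsening or re-operation counts in any primary outcome.

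**The concern.** Some of the removal grounds are close to the outcomes themselves. The primary outcomes include healing time, recurrence to 3 months and total cure, and a patient who worsens or needs another operation is a likely failure on them. Other grounds, such as not receiving the allocated procedure, describe patients whom an ITT analysis exists to keep.

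If these patients stop being observed, their missing data are informative. Imputation from patients who stayed would then tend to make them look like patients who did well. If the two arms lose such patients at different rates, the between-arm comparison is biased. The triggers are partly a matter of judgement: several termination items rest on the investigator's view, and no prescribed range of drugs or operations is set out in the article.

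**Working it through.** **Step 1: do the rules stop treatment or follow-up?** The Intervention description gives one operation per patient, and Trial design puts the intervention within the hospital stay. After discharge no allocated treatment remains to be stopped, so leaving early can only mean leaving follow-up. The Medical treatment paragraph agrees, since it lets observation be ended. For events in hospital the reading is less certain.

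**Step 2: do the rules fit the ITT definition?** ITT is "the intent-to-treat analysis set defined as all randomised patients". The rules do not say that removed patients leave this set, so two readings remain:

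- If they are left out, the ITT set is no longer all randomised patients.
- If they are kept but not observed, their outcomes are imputed.

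The article does not choose between these, and both lose the observed outcome of likely failures.

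**Step 3: the plan's own allowance.** Sample size gives 47 per group, a 10% loss to follow-up, and 52 per group: 47 × 1.10 = 51.7, rounded up to 52. The allowance is 52 − 47 = 5 patients per arm. It is meant for loss to follow-up in general, so 3 to 5 is used below only as a plausible scale.

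**Step 4: illustration for total cure.** Assume 46 of 52 cured in one arm (no cure rate is given for this trial), and assume that every unobserved patient is a failure.

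| Failures unobserved | Left out | Imputed at the rate of those who stayed |
|---|---|---|
| 0 | 46/52 = 88.5% | 88.5% |
| 3 | 46/49 = 93.9% | (46 + 3 × 0.939)/52 = 93.9% |
| 5 | 46/47 = 97.9% | (46 + 5 × 0.979)/52 = 97.9% |

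The shift is 5.4 to 9.4 points. Imputation under missing at random with no informative covariates gives the same expected value as leaving the patients out. If the model uses wound status recorded before removal, the shift is smaller but in the same direction. If both arms have 46/52 and each loses 3 failures, both read 93.9% and the difference stays at zero. Bias in the comparison therefore needs unequal removal.

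**Step 5: illustration for healing time.** The article gives a 10-day difference but no SD. Solving the standard two-sample formula for 47 per group gives SD = 10 × √(47/2)/2.80 = 17.3 days; SD 10 was also tried. Healing times were simulated 20,000 times as lognormal with mean 25 days in both arms and compared with a Welch t-test. The slowest healers of 52 were dropped from one arm only.

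| SD | Dropped | Shift in mean | False-positive rate |
|---|---|---|---|
| 10 | 0 | 0.0 days | 4.8% |
| 10 | 2 | −1.1 days | 10.0% |
| 10 | 5 | −2.2 days | 25.2% |
| 17.3 | 0 | 0.0 days | 4.6% |
| 17.3 | 2 | −2.1 days | 11.3% |
| 17.3 | 5 | −4.0 days | 29.2% |

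This is an extreme case: the slowest patients exactly, one arm only, and no imputation. It shows sensitivity and is not a forecast.

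**The case against.** The strongest reply is that the criteria govern participation and not the analysis set. One section is headed as being about discontinuing interventions, all randomised patients stay in ITT, deviations have their own per-protocol set, and missing values are imputed. A reader might infer that the plan contradicts its ITT definition and deletes treatment failures. The documents do not support that, because nothing in them takes these patients out of ITT.

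Other inferences also go too far:

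- **Safety data are lost.** Observation and recording follows adverse reactions until laboratory values and clinical findings have normalised, and all adverse events are to be recorded.
- **Graft loss leads to removal.** It is not a listed ground. Graft survival is part of the cure definition, so an observed graft loss scores as not cured. Wound infection is assessed in both arms.
- **Surgeons who know the allocation decide.** The criteria name the investigator, and the blinding section says investigators are blinded. Whether that is credible is a separate question.
- **All the grounds are outcomes.** Ineligibility, untruthful information and absence of treatment are not. In addition, inclusion is not always clearly the same moment as randomisation.

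The imputation model and sensitivity analyses may properly sit in an analysis plan that is not shown, so their absence is not the point here. What the objection does not answer is that the article itself fixes rules that can end observation on outcome-related grounds. A later analysis plan can score such patients, but it cannot recover visits that were never made.

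**Conclusion.** The concern holds as an unreconciled tension with a risk of informative missingness. Followed as written, the removal rules can leave likely failures without cure, recurrence and healing-time data, and the stated remedy is imputation. The risk of bias between arms depends on removals being related to outcome and unequal between arms.

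Its size cannot be determined, since no cure rate, SD or removal count is given. The 88% to 94–98% illustration rests on an assumed 46/52, on every unobserved patient being a failure, and on loss in one arm only. It applies to total cure and not to cure at 14 days. For scale, the Background puts healing after fistulotomy above 90%, which leaves under 10 points of room for improvement, so even a modest artefact would matter.

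**What to change.** Reconcile the criteria with the analysis section as follows.

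1. State that meeting any withdrawal, rejection, shedding or termination criterion does not remove a patient from ITT, and that outcome collection continues to month 6 unless consent is withdrawn.
2. In ITT, count as not cured a re-operation for the wound or fistula, and a removal for worsening or a procedure-related serious adverse reaction before documented healing. State how the same events count for recurrence.
3. In the healing-time analysis, treat such patients as unhealed through the end of follow-up, without censoring them at removal. The listed t-tests cannot hold an unhealed patient, so a rank-based or time-to-event comparison is needed.
4. Limit multiple imputation to loss unrelated to outcome, and add a sensitivity analysis that counts every missing patient as not cured.
5. Use the rejection and shedding criteria only to define the per-protocol set, settled before unblinding.
6. Report removals by arm and reason.

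The cost is mostly wording, plus a healing-time method that accepts unhealed patients; the visits are already in the schedule. Scoring removals as failures is a conservative convention and may make either arm look slightly worse. Trial status expected completion by 24 October 2022, before the article appeared on 22 July 2023, so further visits may no longer be possible. In that case items 2 to 6 still apply. Nothing here bears on when clinical care should be stopped or changed.
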